#### Analysis of cost-effectiveness

A detailed Discrete Event Simulation model, with costs and outcomes summarised at 30 days, 90 days and 10 years, was developed to assess the cost effectiveness of the new London stroke model implemented in 2010
[33]. Following successful implementation of the model(s), and a sufficient period of time to collect adequate patient numbers, we will populate the model using the data sources mentioned above in *Data Collection*, for London and Greater Manchester ‘before’ and ‘after’ implementation. Costs will be assessed from the perspective of the NHS and personal social services (PSS). The proposed cost-effectiveness measure in the short run model is the incremental cost per death avoided at 90 days; in the long run it is the incremental cost per quality adjusted life year gained. Cost components will include: ambulance; scans; thrombolysis; length of stay on wards; and discharge destination. Cost-effectiveness will be calculated as the mean cost difference between the comparators divided by the mean difference in outcomes (90 day mortality/QALYs) to give the incremental cost-effectiveness ratio (ICER). We will undertake deterministic (one-, two- and multi-way) and probabilistic sensitivity analysis.

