## Design/methods

### Design

#### Understanding what works and at what cost

Identifying what process and outcome changes have occurred, and at what cost, provides evidence about the extent to which the reconfigurations have succeeded in their objectives of changing the system of service provision and quality of care. This component of the evaluation will analyse documentary evidence to establish the models applied in London and Greater Manchester; it will also identify whether any changes in process and outcomes can be associated with these changes.

In assessing the nature and results of the two reconfigurations, the evaluation will apply a controlled before-and-after design
[24]. This will compare the London and Manchester models in terms of the impact they had on processes, outcomes, and costs of care. In addition to comparing London with Greater Manchester pre- and post-reconfiguration, the analysis will make a wider comparison with the rest of England. This approach will permit observed changes to be analysed in the context of changes that take place in the rest of England over this period. A two-step approach will be taken to the analysis of outcomes: in the first instance, the impact of the reconfigurations on mortality and length of stay will be investigated; if evidence of impact on these is found, a more detailed cost-effectiveness analysis will be undertaken.

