First, the reconfigurations took place at slightly different times, and took different trajectories, with Greater Manchester taking a more phased approach than occurred in London. Therefore, as the reconfigurations have different ‘before’ and ‘after’ phases, it is possible that external factors—such as participation in national audits—might have influenced the two reconfigurations differently. Also, conclusions drawn about the relationship between reconfiguration and any improvements seen are less clear in ‘before’ and ‘after’ studies. It is possible that any improvements that occur could have occurred anyway and not as a direct result of the policies implemented. Without any randomisation, it is also harder to rule out potential biases and gaming, such as admitting less complex patients. However, these complexities reflect the ‘real world’ nature of service reconfiguration, and change more broadly, and are thus likely to be faced quite commonly in evaluations of this kind. As our research design actively seeks to analyse such contextual influences, this in fact represents an opportunity to improve understanding of the relationship between national (‘macro’) drivers for improvement and organisational (‘meso’) responses to these.

The retrospective nature of this evaluation impacts on the qualitative component of the research. For example, planning and implementation events could not be observed; in addition, interviewees’ recollection of events will naturally vary. Ensuring suitable representation of stakeholders—based on documentary analysis—and applying Patton’s validity criteria
[35] in the analysis will be key to ensuring that important lessons are not missed. In terms of studying patient experience, only patients who have recently experienced reconfigured services will be interviewed, so that no ‘before’ equivalent will be available. However, we will compare these patient experience data with literature on the experiences of stroke patients and carers
[36,37], so that the analysis can examine whether patients’ concerns have been addressed by changes brought about by the reconfigurations.

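### The cost-effectiveness analysis does not define its comparators or use the rest-of-England-controlled effect, so as written the value-for-money ICER can include national secular change

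*Protocol article*

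**What the plan says.** Under Design (Understanding what works and at what cost), the article states that "the evaluation will apply a controlled before-and-after design". The stated purpose is to "compare the London and Manchester models in terms of the impact they had on processes, outcomes, and costs of care". A wider comparison with the rest of England is added so that observed changes can be read "in the context of changes that take place in the rest of England over this period". Cost-effectiveness is the second step of this same two-step analysis.

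The Econometric analysis section gives a regression with region and year terms and a reconfiguration indicator whose coefficient is α3. A favourable α3, for mortality and/or length of stay, triggers the cost-effectiveness analysis.

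The Analysis of cost-effectiveness section then says the simulation model will be populated from the routine data sources "for London and Greater Manchester ‘before’ and ‘after’ implementation". The ICER is defined as follows: "Cost-effectiveness will be calculated as the mean cost difference between the comparators divided by the mean difference in outcomes", the outcomes being 90-day mortality in the short run and QALYs in the long run. On uncertainty it says: "We will undertake deterministic (one-, two- and multi-way) and probabilistic sensitivity analysis".

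**The concern.** A controlled before-and-after study exists to separate the effect of the intervention from change that was happening anyway. The cost-effectiveness section names two regions at two times as the model's data. It does not mention the rest of England, a trend adjustment, or α3 as an effect input. For question 4 (value for money), the natural contrast from those inputs is after versus before within a region. That compares then with now, not with reconfiguration against without it.

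At stake is the main economic conclusion. Deaths avoided, QALYs gained and bed-days saved could each contain national change, and the ICER could disagree with the study's own controlled effect estimate. The Discussion recognises the general hazard: "It is possible that any improvements that occur could have occurred anyway and not as a direct result of the policies implemented". That remark is a limitation of the study as a whole. It is not carried into the ICER.

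**Working it through.** The article states no ICER, effect size or national trend, so there is no figure of its own to reproduce. The check has two parts.

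**1. The sections side by side**

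- Design: controlled, rest of England included, scope covers processes, outcomes and costs.
- Econometric analysis: region and year terms; α3 is the effect of interest and the trigger for the next step.
- Analysis of functional independence: says the econometric regression will be applied.
- Analysis of process changes: says the same, and repeats the rest-of-England comparison.
- Analysis of cost-effectiveness: says neither. It names London and Greater Manchester before and after, and undefined comparators.

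There is also a mismatch of inputs. The short-run ICER uses 90-day mortality, but the mortality outcomes listed under Data collection are in hospital, at 30 days and at one year. The outcomes named for the regression are mortality and length of stay; none is named for the other cost components. The controlled estimates as listed therefore could not pass straight into the ICER.

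**2. The algebra**

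Let dC and dE be the true cost and effect of reconfiguration, and c and s the secular changes in cost and effect over the same interval.

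- Controlled ICER = dC/dE
- Within-region before/after ICER = (dC + c)/(dE + s)
- Share of the apparent benefit that is secular = s/(dE + s)

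For positive dC and dE, and positive dE + s, the before/after ICER is too low when c/dC < s/dE and too high when c/dC > s/dE.

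Illustration only; every input is an assumption. Take dC = £1,000 per patient and dE = 1 percentage point fewer deaths at 90 days. The controlled ICER is 1,000/0.01 = £100,000 per death avoided.

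| s (points) | c (£) | Before/after ICER (£) | Ratio to controlled | Secular share of benefit |
|---|---|---|---|---|
| 0 | +500 | 1,500/0.010 = 150,000 | 1.50 | 0% |
| 0.5 | 0 | 1,000/0.015 = 66,667 | 0.67 | 33% |
| 0.5 | +500 | 1,500/0.015 = 100,000 | 1.00 | 33% |
| 1 | 0 | 1,000/0.020 = 50,000 | 0.50 | 50% |
| 1 | +500 | 1,500/0.020 = 75,000 | 0.75 | 50% |
| 1 | −500 | 500/0.020 = 25,000 | 0.25 | 50% |
| 2 | 0 | 1,000/0.030 = 33,333 | 0.33 | 67% |
| 3 | 0 | 1,000/0.040 = 25,000 | 0.25 | 75% |

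The third row shows that the two secular components can cancel in the ratio even though a third of the apparent benefit is not due to reconfiguration.

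**The gate.** With dE = 1 and s = 1, a correctly estimated α3 shows a fall of 1 point and the analysis runs, but a before/after denominator is 2 points. The trigger can also be met on length of stay alone. If mortality were then unaffected, the whole before/after fall in deaths would be secular.

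**The case against.** The strongest defence is that this is silence in a condensed article. The section does not say that the inputs are raw, that the control is dropped, or which arms the comparators are. The Design section promises a control in general terms, includes costs, and makes cost-effectiveness a step of the same analysis. The simulation model is published separately, and its arms may be parameterised in a way that cannot be seen here. The α3 gate should keep the analysis from running when the gain is wholly national. If the comparison were London's change against Greater Manchester's, a common trend would largely cancel.

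Much of this stands. A reader might infer that unadjusted data are certain to be used and that the control has been abandoned; the text supports neither. A reader might also infer that the bias must favour reconfiguration, but a secular cost rise can push the ICER the other way. And a reader might convert an assumed annual fall in mortality, applied to pooled 2004 to 2013 data, into a yearly count of wrongly credited deaths or a fold-overstatement. The document gives no such trend and does not say that the model will pool that whole window.

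What does not stand is the conclusion that nothing needs changing. The section goes beyond silence: it states the populations and the formula, and followed literally these conflict with the Design section. The gate screens for a favourable result but does not correct the size of the ICER. The sensitivity analyses are listed by type, with no counterfactual or trend scenario among them. A London-versus-Manchester contrast may serve question 5 but not question 4, and the Discussion notes that the two regions have different before and after phases, so a common trend need not cancel fully.

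**Conclusion.** The point holds as an inconsistency in what is specified. The cost-effectiveness section leaves its comparators undefined and does not carry the controlled effect into the ICER, although the Design section promises control for costs as well as outcomes. Taken literally, the answer to question 4 is an uncontrolled within-region contrast that may include national change.

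Neither the magnitude nor the direction can be derived from the document. In the illustration, with no secular cost change and s from 0.5 to 3 points, the before/after ICER is 0.67 to 0.25 of the controlled value; with no secular mortality change and a £500 cost rise it is 1.5 times that value. These results depend wholly on the assumed dC, dE, s and c, and on after versus before being the contrast used.

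**What to change.** State the comparator as the after period without reconfiguration, separately for London and Greater Manchester. Build it by removing region-specific difference-in-differences estimates, with the rest of England as control, from the observed after values. Do this for 90-day mortality, length of stay, discharge destination and thrombolysis, and add 90-day mortality to the regression outcomes. Apply the method to inputs available nationally; for cost components with no named national source, such as ambulance and scans, state the assumption made.

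Draw these estimates with their uncertainty in the planned probabilistic sensitivity analysis. For question 5, compare the regions on net increments. Keep the plain before/after ICER as a labelled descriptive or sensitivity result.

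The cost is a few extra regressions, largely on the HES, ONS and audit data already planned for the controlled analyses, and some wording. The ICER will be less precise and may look less favourable.

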### Data collection

#### Understanding what works and at what cost

To establish what models were applied and how they were developed and put into action in London and Greater Manchester, the evaluation will analyse a range of documentary evidence. This will include project board papers, service designation criteria, and tariff documentation.

Using routinely collected data, the evaluation will assess whether the reconfigurations were associated with changes in process, outcomes, and costs of care. Data will be collected retrospectively from 2004, up to the point at which services began to change; while ‘after’ data will be collected from the points at which the new models were fully in place, through to December 2013.

Care process measures have been selected for the evidence indicating relevance to quality of care and their positive association with improved outcomes
[28-30]. Measures include proportion of patients appropriately receiving thrombolysis, admitted to a stroke unit for 50% of their stay, appropriately receiving aspirin in the acute period, assessed by a multidisciplinary team, and receiving a swallowing test within the first 24 hours of care. These data will be drawn from national data sources (the Royal College of Physicians’ Sentinel Stroke Audit, the Stroke Improvement National Audit Programme (SINAP), and the Sentinel Stroke National Audit Programme (SSNAP)).

Outcome measures will include patient’s length of hospital stay, discharge destination, readmission rates, and mortality (in hospital, at 30 days, and at one year); these data will be drawn from HES and ONS datasets. Patient’s independent function (measured through Barthel Index score at discharge, and/or Modified Rankin score) will be drawn from Sentinel audit data, SINAP and SSNAP.

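### The short-run ICER rests on 90-day mortality, which is neither a named outcome time point nor tied to the regression that controls for national trends

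*Protocol article*

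**What the plan says.** Under Data collection (Understanding what works and at what cost), the article lists the outcomes: "Outcome measures will include patient’s length of hospital stay, discharge destination, readmission rates, and mortality (in hospital, at 30 days, and at one year". For their source it says "these data will be drawn from HES and ONS datasets". Data for the after period run "from the points at which the new models were fully in place, through to December 2013".

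The Design section describes a controlled before-and-after study, with the rest of England added so that changes in the two regions can be read against national change. The Econometric analysis section gives the regression. Its outcome is described only as mortality or length of stay, and a favourable coefficient for reconfiguration (α3) opens the economic analysis. No mortality time point is named there.

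The Analysis of cost-effectiveness section describes an existing discrete event simulation "with costs and outcomes summarised at 30 days, 90 days and 10 years". It says "we will populate the model using the data sources mentioned above in" the Data collection section, for London and Greater Manchester before and after implementation. The short-run measure is stated as "The proposed cost-effectiveness measure in the short run model is the incremental cost per death avoided at 90 days". The cost difference is "divided by the mean difference in outcomes (90 day mortality/QALYs) to give the incremental cost-effectiveness ratio (ICER".

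**The concern.** The article names one set of mortality time points for measurement and a different one for valuation. On its own that would be a small gap in labelling. It matters because of what goes into the ratio. The regression is the only place where national change is removed, and nothing links the 90-day figure to it. The simulation inputs are described for the two reconfigured regions alone.

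The Discussion accepts that improvements might have happened without the reconfigurations. If stroke mortality was falling across England, an uncontrolled before/after difference would count that fall as deaths avoided by reconfiguration. This bears on research question 4 (value for money) and research question 5 (whether London's extra investment bought better outcomes than Manchester's).

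**Working it through.** The article states no event rate, sample size or effect size on this point, so there is no figure to reproduce. The check compares sections, then uses short algebra and some calendar arithmetic.

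**1. Time points, section by section**

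- Data collection: in hospital, 30 days, one year.
- Econometric analysis: mortality, with no time point.
- Analysis of cost-effectiveness, simulation summaries: 30 days, 90 days, 10 years.
- Analysis of cost-effectiveness, short-run ratio: 90 days.

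Ninety days appears only in the cost-effectiveness section. Of the simulation's three summary points, only 30 days is also in the outcome list.

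**2. Comparators, section by section**

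- Design and Econometric analysis: London, Greater Manchester and the rest of England.
- Analysis of cost-effectiveness: London and Greater Manchester, before and after.

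**3. What this does to the denominator**

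For a region, let D be the before/after fall in 90-day mortality, and T the fall in the rest of England over the same calendar periods. Assuming the region would otherwise have followed the national trend, the controlled fall is D − T.

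- Ratio as written: ΔC / D.
- Ratio using the controlled effect: ΔC / (D − T).
- With f = T / D, the second equals the first divided by (1 − f).

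For a given positive cost difference ΔC and f between 0 and 1, the ratio as written is therefore too low by a factor of 1 − f. If national mortality was flat, f = 0 and nothing changes. If it rose, the bias reverses. The article gives neither D nor T, so f cannot be filled in.

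**4. Does the trend cancel when London is set against Greater Manchester?**

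The difference between the two before/after falls contains T(London) − T(Manchester). It cancels only if the two regions share the same before and after windows. The Discussion says that the windows differ.

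**5. The December 2013 date**

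The last admission with complete follow-up, if deaths are also cut off on 31 December 2013, is:

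- 30 days: 1 December 2013
- 90 days: 2 October 2013
- 365 days: 31 December 2012

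The article dates the London model to 2010. If London's after period starts somewhere between 1 January and 31 December 2010 (an assumption), it lasts 48 to 36 months. Admissions without full one-year follow-up would then be 12/48 = 25% to 12/36 = 33% of it, and those without full 90-day follow-up about 3/48 = 6% to 3/36 = 8%. If December 2013 is only the last admission month and deaths are captured beyond it, both shares are zero.

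**The case against.** The strongest reply is that nothing is missing except a label. The outcome list is open, since it says what the measures will include. Ninety-day death can be derived from the HES and ONS data already named, and the regression's unspecified mortality outcome does not exclude it. Ninety-day mortality is also an output of the simulation, and the article never says that the ICER denominator comes from α3.

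Most of this is right, and it rules out two stronger readings. A reader might infer that 90-day deaths are not collected, or that a controlled 90-day effect cannot exist. The open list and the named data sources do not support that. A reader might also infer that 30-day or one-year mortality opens the economic analysis. The gate names no time point.

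The reply does not dispose of the link to the control group. It confirms that the ratio, as described, is populated from regional before/after data and not from the controlled estimate. One can say that this confounding issue would remain if 90 days were on the list. That is true, and it is why listing the time point alone would not be enough.

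A third stronger reading is that one-year mortality for 2013 admissions will be understated and counted as benefit. The text does not establish this. It does not say that December 2013 cuts off deaths. The parallel before period ends when services began to change, which describes a period of care and not a limit on follow-up. Nor is one-year mortality named as an input to the simulation. In the regression, the rest of England would be truncated in the same calendar year, so the year term would absorb most of any such effect. A condensed article may also leave extraction dates to the full protocol.

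**Conclusion.** The point holds in this form: the short-run ratio uses a mortality time point absent from the named outcomes and not tied to the controlled regression, and its inputs are described for the two reconfigured regions only. The denominator could therefore include national mortality change that the design set out to remove.

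The effect on the ratio is the factor 1 − f derived above. It rests on a positive cost difference and on the region otherwise following the national trend. Its value is unknown from the article, and it may be negligible if national 90-day mortality was stable. The change is still worth making, because it affects research questions 4 and 5 and the data are already to hand.

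The December 2013 date is a conditional clarification and not a demonstrated error, so no bias figure should be attached to it.

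**What to change.** - Derive 90-day all-cause mortality from the HES and ONS data and add it to the outcome list.
- Fit the regression of the Econometric analysis section to it, with the rest of England included and a separate reconfiguration effect for London and for Greater Manchester.
- Use that region-specific controlled estimate, with its uncertainty carried into the probabilistic sensitivity analysis, as the mortality difference in the short-run ICER.
- Name the mortality time point used to decide whether the economic analysis goes ahead.
- State whether December 2013 limits admissions only or also the capture of deaths. If it limits deaths, restrict one-year mortality to admissions through December 2012 or obtain deaths to December 2014, and restrict 90-day mortality to admissions through 2 October 2013 or obtain the later deaths.

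The cost is one more derived variable from data already named, one more regression outcome and a few sentences of text. The ratio may look less favourable once national change is taken out. If deaths do stop at December 2013 and are not extended, the one-year analysis loses the 2013 admissions.
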